**Data safety monitoring plan**

The sedatives and analgesics that are planned to be used in this study are widely used for sedation during ERCP and considered relatively safe. Data safety monitoring will be done by the primary investigator every 50 cases by comparing reference papers, CRFs and study protocol in order to guarantee the integrity of collected data, and review safety date of enrolled patients.

**Study end point**

1. Primary end point
   1. Recovery time (time from scope withdrawal to full recovery)
   2. Adverse event during and after procedure
      1. Desaturation (SaO2 < 90% for > 10 sec, need for jaw thrust) rate
      2. Apnea (cessation of respiratory activity for > 30 sec under visual observation)
2. Secondary end point
   1. Overall satisfaction with sedation and procedure by endoscopist (VAS, 0 ~ 100)
   2. Overall satisfaction with sedation by patients (VAS, 0 ~ 100)

**Statistical analysis**

Continuous variables will be analyzed with either the independent two sample t-test or the Mann-Whitney U Test depending on distribution. Categorical variables will be analyzed by the Chi-square or Fisher’s exact test. A P value of < 0.05 is defined as statistically significant.

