**Sample size calculation**

Based on a previous study that compared sedation methods for ERCP (2), 100 patients are needed in each group in order to detect a 20% difference in recovery time between the two groups at a significance level of 0.05 and 85% power (α=0.05, 1-β(power)=0.85) considering a type I error of 0.05.

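### Several primary endpoints share an unadjusted 5% threshold with no success rule, and the sample size covers recovery time only

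*Protocol*

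**What the plan says.** The Protocol's Study end point section has two numbered items under the primary heading. The first is recovery time. The second is "Adverse event during and after procedure", which has two sub-items, desaturation and apnea, each with its own definition. The section defines no composite and no order of testing, and it does not say whether one or all of these must be positive.

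The Statistical analysis section assigns a t-test or Mann-Whitney test to continuous variables and a chi-square or Fisher's exact test to categorical ones. It closes with a single rule: "A P value of < 0.05 is defined as statistically significant".

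The Sample size calculation section sets 100 per group. The only target it gives for that number is: "detect a 20% difference in recovery time between the two groups at a significance level of 0.05 and 85% power". It refers to one earlier study for its basis. No expected rate, target difference or power for desaturation or apnea appears anywhere in the Protocol.

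**The concern.** The three sections do not fit together. One names several primary endpoints, one sizes the trial for a single endpoint, and one tests all of them at the same unadjusted level. The reader cannot tell what result would make the trial positive, and neither possible answer leaves the design figures intact:

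- **Any one primary suffices.** The chance of at least one false positive among the primaries exceeds 5%.
- **All primaries are required.** The 85% is the power of one component, not of the trial.

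The stake is interpretive. The study aim is broad (clinical outcome and satisfaction), so without a rule fixed in advance a single significant primary could be presented as the trial's result. A non-significant desaturation or apnea comparison could also be taken as evidence of equal safety, although the trial was not planned to show that.

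**Working it through.** **Inputs from the Protocol:** "α=0.05, 1-β(power)=0.85"; 100 per group; a 20% difference in recovery time; chi-square or Fisher's test for events. **Not given, so assumed:** two-sided testing, the SD/mean of recovery time, and all event rates.

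**1. The plan's own figure.** The Protocol gives no mean or SD, so 100 per group can be neither confirmed nor refuted. The standardised difference detectable with 100 per group is

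d = (1.960 + 1.036) × √(2/100) = 0.424.

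A 20% difference therefore implies SD/mean = 0.20/0.424 = 0.47. With n = 2(1.960 + 1.036)²(CV/0.20)²:

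| SD/mean | n per group |
|---|---|
| 0.40 | 72 |
| 0.47 | 100 |
| 0.50 | 113 |
| 0.60 | 162 |

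The stated size is attainable for recovery time, and only for recovery time.

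**2. Family-wise error if any one primary suffices.**

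- Three independent tests: 1 − 0.95³ = 14.3%.
- Ceiling under any dependence: 3 × 0.05 = 15%.
- Desaturation and apnea correlated 0.3 to 0.7 (simulation): 14.0% to 12.9%.
- Adverse events as one composite, two tests: 1 − 0.95² = 9.75%, at most 10%.
- Fisher's test is conservative. At 100 per group its actual size is 0.5%, 2.9% and 3.3% for event rates of 2%, 10% and 20%. If it is used for both event endpoints, with independence, the total is 1 − 0.95 × 0.995² = 5.9%, 1 − 0.95 × 0.971² = 10.4% and 1 − 0.95 × 0.967² = 11.2%.

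**3. Power if all primaries must succeed.** Each test at 0.05 is then sufficient for error control. Joint power cannot exceed that of the weakest component, so it is at most 85%. As an illustration, suppose both event endpoints were truly 20% vs 10%, with power 52% each (step 4). Joint power would be at most 52%, and 0.85 × 0.52 × 0.52 = 23% under independence.

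**4. Power for a single event endpoint at 100 per group, two-sided 0.05.** The method sums the binomial probabilities of all pairs of event counts (i, j) for which the test rejects. For the uncorrected chi-square test this means |i − j|/100 ÷ √(p̄(1 − p̄) × 2/100) > 1.96, where p̄ = (i + j)/200.

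| Assumed rates | Chi-square | Fisher |
|---|---|---|
| 10% vs 8% | 8% | 5% |
| 20% vs 16% | 12% | 8% |
| 10% vs 5% | 27% | 19% |
| 20% vs 10% | 52% | 44% |
| 30% vs 15% | 73% | 67% |
| 40% vs 20% | 88% | 84% |
| 20% vs 5% | 92% | 88% |
| 30% vs 10% | 96% | 94% |

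**5. Precision.** The approximate 95% half-width for the risk difference is 1.96 × √(2p(1 − p)/100). It is 8 percentage points at p = 10% and 11 at p = 20%.

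**6. Cost of an alpha split instead of an ordering.** With the back-solved SD/mean of 0.472, recovery-time power at 0.05/3 falls from 85% to about 73%, and about 132 per group would restore it. At 0.05/2 the power is about 77.5%, and about 120 per group would be needed.

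**The case against.** Several points on the other side have weight.

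- **The Protocol never claims a family-wise 5%.** The 0.05 and the 85% in the Sample size calculation section belong to the recovery-time comparison. This stands: those figures are not false for that comparison. What is missing is any link between them and the longer list of primaries.
- **No success rule is stated.** A reader might infer that the trial may claim success on any of three endpoints. The Protocol does not say so. If all were required, there would be no inflation. The 14% is therefore conditional.
- **Three is not the only count.** Adverse events are one numbered item and could be analysed as a composite. Separate definitions make three the natural reading, but two is possible.
- **Low power is not established.** A reader might infer that desaturation and apnea are almost unpowered, or that realistic differences cannot be detected. The Protocol gives no rates and does not say what is realistic, and the 20% difference is specified only for recovery time. Power from 8% to 96% over assumed rates does not support either statement.
- **A statistical analysis plan, not available here, may settle multiplicity.** That is possible, and an absent adjustment alone would not be a finding. But the Protocol itself names several primaries, sets one flat threshold and sizes one endpoint, and those statements need reconciling where they stand.
- **Desaturation and apnea are part of the scientific motivation.** The Background names both as drawbacks of propofol alone. Demoting them is therefore a real choice, and an ordering that keeps them primary serves equally well.

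**Conclusion.** The concern holds in conditional form. The Protocol fixes several primary endpoints and a flat 0.05 without a success rule, and it supports only recovery time with a sample size.

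Under an any-one-suffices rule, the family-wise error is about 14% for three independent tests and cannot exceed 15% if each test holds its nominal level. It falls with positive correlation or Fisher's test, and is 9.75% for two independent tests. Under an all-required rule the error is controlled, but the trial's power is unstated and no higher than 85%.

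For desaturation and apnea the documents support only this: no power is stated or justified, and it would be low for uncommon events or modest effects. The event rates used above are assumptions, as are two-sided testing and the back-solved SD/mean. The error figures in the any-one case rest on independence where so marked.

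**What to change.** State the decision rule in the Protocol:

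1. Test recovery time first, two-sided at 0.05. It is the only endpoint that was sized.
2. Only if it is significant, test desaturation and then apnea for formal claims, each at 0.05 in that fixed order. Alternatively, apply Holm between the two (smaller P value against 0.025, the other against 0.05).
3. Label desaturation and apnea either as key secondary endpoints or as hierarchically ordered primaries. Both labels are acceptable, and the ordering is what controls the error. If adverse events are meant as one composite, define it and give it a single place in the order.
4. Report both as risk differences with 95% confidence intervals whatever the recovery-time result, and state that a non-significant difference will not be read as equal safety.

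This is about one paragraph. It keeps the full 0.05, and hence the planned 85% power, for recovery time and needs no extra patients. The price is that desaturation and apnea lose stand-alone confirmatory status: if recovery time is not significant, no formal claim on either can follow. If that is unacceptable, the alternative is a stated alpha split, with assumed event rates and a sample size for each primary, at the cost shown in step 6 of the working.
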